##### Perinatal secondary outcomes

Number of stillbirths per 10,000 deliveries per month.

Number of neonatal deaths per 10,000 deliveries per month.

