#### Primary outcome

The rate of a composite of maternal mortality or major morbidity (one of maternal death, eclampsia or emergency hysterectomy with no double counting per 10,000 deliveries in each cluster each month). We will report the effect of the intervention on the primary endpoint, on each of the three components, and on each of the secondary endpoints.

*Maternal death* was defined as death during pregnancy or within 42 days of delivery (or last contact day if contact not maintained to 42 days).

*Eclampsia* was defined as occurrence of generalised convulsions with increased blood pressure during pregnancy, labour or within 42 days of delivery in the absence of epilepsy or another condition predisposing to convulsions.

*Emergency hysterectomy* was defined as surgical removal of all or part of the uterus.

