### Sample size calculation

Sample size estimation has been carried out by the CRADLE statistician, using Stata version 13.1 and the methods of Hemming and Girling [16]. This was informed by data from the feasibility phase. For the purpose of the power calculation an assumption that there are at least 4000 deliveries per centre per month was made (or 8000 per cluster period of 2 months) and at least nine clusters, each observed for 20 months (10 time periods of 2 months each). We anticipated a baseline event rate of 1% and anticipate a 25% reduction in this to 0.75% post intervention. We would require a total of 6300 outcome events, with a coefficient of variation of 0.4 and an Intra Cluster Correlation of 0.0085, to have power of 99%. We would require a total of 2450 outcome events with a coefficient of variation of 0.4, to have power of 95%.

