### Statistical plan

The effect of the intervention on the primary outcome, on each of the three components, and on the secondary outcomes specified above, will be reported. Results will be reported firstly as odds ratios (ORs), with risk ratios (RRs) as a secondary comparison if the appropriate models converge. Within the stepped-wedge cluster design it remains appropriate to analyse outcome data from clusters individually, despite randomising cluster time points with some clusters paired [17].

The main statistical analysis method will be by logistic regression, using generalised estimating equations with a population-averaged model [18] (Stata command xtgee) with fixed centre effects and separate fixed linear trends in each centre for changes in outcome over time. Autoregressive correlation will account for decreasing correlations between observations over time. This model outperformed the multilevel model structure of Hussey and Hughes [19], being apparently less susceptible to bias. It gives equal weight to each woman, rather than each centre, and (being population-averaged) reports effects averaged over the length of the trial. Simulations studies suggest that using time categories, rather than linear trends do not correct well for separate time trends by centre, and can cause convergence problems. Results will be expressed as ORs; at the low event rates expected (≤ 5%), ORs and RRs are reasonably close (in the simplest case, for 5% and 3.75%, RR = 0.75, OR = 0.74). A secondary analysis to obtain RRs using a log link will be attempted, but simulation studies suggest that the convergence may be poor. We will adjust for centre effects and linear time trends and the interaction between them. This will effectively adjust for differences in baseline availability of resources between clusters.

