A composite of maternal mortality or morbidity (one of maternal death, eclampsia or emergency hysterectomy with no double counting) was chosen as the primary outcome as powering a trial for maternal death alone would require a prohibitively large sample size. These are robust and meaningful clinical endpoints that are unambiguous and, therefore, feasible to collect in these environments. Maternal complications were selected, each of which is associated with significant acute and chronic morbidity. Therefore, a reduction in this composite would be highly desirable. Each component of the primary outcome will be individually interrogated to ensure no paradoxical effects within the composite, i.e. an increase in morbidity may be associated with a reduction in mortality, as a consequence of intervention. Therefore, should the CRADLE intervention result in appropriate referral and intervention (e.g. hysterectomy) this will be recognised as beneficial even though the overall effect on the composite outcome may be neutral. We have ensured that all primary outcome measures are feasible to collect at primary to tertiary facilities, as determined through the feasibility study. It is, therefore, not necessary to conduct costly household surveys. In the unlikely event that a primary outcome occurs without HCP contact, this is likely to be unchanged pre and post intervention and should not affect our ability to assess the impact of intervention implementation.

It is recognised that the CRADLE intervention may reduce perinatal mortality and morbidity. Perinatal outcomes have not been included as primary outcomes as the intervention is designed specifically to identify maternal health complications. Many of these occur postpartum and will not directly influence perinatal outcomes. Acquisition of detailed perinatal data within LMIC settings would be a substantial additional cost. However, the secondary perinatal outcomes will be collected in women who experience a primary outcome.

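### Stillbirth and neonatal death are defined per 10,000 deliveries but, per the Discussion, collected in women with a primary outcome; rates and effects built that way do not describe perinatal mortality

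*Protocol article*

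**What the plan says.** Four statements in the Protocol article bear on this.

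- **Definition (Perinatal secondary outcomes).** The two outcomes are "Number of stillbirths per 10,000 deliveries per month" and "Number of neonatal deaths per 10,000 deliveries per month". Neither is limited to a subgroup.
- **Collection (Discussion).** The article gives a cost reason, "Acquisition of detailed perinatal data within LMIC settings would be a substantial additional cost", and continues: "However, the secondary perinatal outcomes will be collected in women who experience a primary outcome".
- **Use (Primary outcome; Statistical plan).** The first section says "We will report the effect of the intervention on the primary endpoint, on each of the three components, and on each of the secondary endpoints". The second repeats the commitment: the effect on the primary outcome, "on each of the three components, and on the secondary outcomes specified above, will be reported". Neither exempts the perinatal outcomes.
- **Planned event rates (Sample size calculation).** "We anticipated a baseline event rate of 1% and anticipate a 25% reduction in this to 0.75% post intervention".

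The Data collection section lists registers, patient records and active case finding as sources. It does not describe a count of stillbirths or neonatal deaths across all deliveries.

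**The concern.** The denominator is every delivery, while the numerator, on the Discussion's account, comes from women who died, had eclampsia or had an emergency hysterectomy. Those are the events the intervention is meant to prevent. When such an event is averted, the woman leaves the group in which a perinatal death would be recorded, whether or not her baby survives. A fall in the primary outcome can therefore appear as a fall in stillbirths per 10,000 deliveries although no baby was saved.

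Two misreadings are at stake. The level could be taken for a perinatal mortality rate when most deliveries cannot contribute to it. The effect could be taken for a perinatal benefit. The second is the more serious, because the Discussion expects that the intervention may reduce perinatal mortality and addresses policy-makers. The cost consequence analysis also draws on health outcomes recorded in the trial, so the figure could carry over into it.

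**Working it through.** **Inputs from the Sample size calculation.** Control event rate p0 = 0.01; intervention rate p1 = 0.0075; at least 9 clusters, 10 periods, 8000 deliveries per cluster-period.

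**Input not in the documents.** q, the risk of stillbirth (or of neonatal death) among women with a primary outcome. It is varied below. Singleton births are assumed.

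**1. Reproduce the plan's own figure.** Deliveries: 9 × 10 × 8000 = 720,000. Mean event rate: (0.01 + 0.0075)/2 = 0.00875. Events: 720,000 × 0.00875 = 6300, the total stated for 99% power. This is also the number of women in whom perinatal outcomes would be collected if the Discussion governs.

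**2. The rate as collected.** Rate per 10,000 deliveries = 10,000 × p × q.

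| q (assumed, same in both conditions) | Control | Intervention | Ratio |
|---|---|---|---|
| 0.10 | 10 | 7.5 | 0.75 |
| 0.20 | 20 | 15 | 0.75 |
| 0.30 | 30 | 22.5 | 0.75 |
| 0.40 | 40 | 30 | 0.75 |
| 1 (ceiling) | 100 | 75 | 0.75 |

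The ratio is (p1 × q)/(p0 × q) = 0.0075/0.01 = 0.75 for any constant q.

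**3. The same case with all deaths counted.** Assume 200 stillbirths per 10,000 deliveries and q = 0.20, and suppose that women whose primary event is averted keep that same risk.

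- Control: 20 recorded + 180 unrecorded = 200.
- Intervention: 15 recorded + 185 unrecorded = 200.

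The recorded ratio is 15/20 = 0.75. The true ratio is 200/200 = 1.00.

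**4. What would cancel it.** In general the recorded ratio is (p1/p0) × (q1/q0). It equals 1 when q1/q0 = 0.01/0.0075 = 1.33. For example, q rising from 0.20 to 0.267 gives 10,000 × 0.0075 × 0.267 = 20 per 10,000 again.

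**5. Share of all perinatal deaths captured.** Share = p0 × q / overall risk, at control rates.

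- Assumed overall stillbirth risk 2–3% and q 20–30%: from 0.01 × 0.20/0.03 = 6.7% to 0.01 × 0.30/0.02 = 15%.
- Assumed overall rate 100–400 per 10,000 and q 0.1–0.4: from 100 × 0.1/400 = 2.5% to 100 × 0.4/100 = 40%.

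**6. Would the artefact be visible?** With 360,000 deliveries per condition (half of 720,000) and clustering ignored, a two-proportion comparison of 10 with 7.5 per 10,000 (q = 0.10) has about 95% power at two-sided 5%. Clustering would change this figure, so it is only a guide.

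**7. What a full count could show.** If S is the all-delivery rate per 10,000, and every perinatal death among the 100 − 75 = 25 averted cases were truly prevented, the ratio would be (S − 25q)/S. With S = 100 and q = 0.3 this is 92.5/100 = 0.925. With S = 400 and q = 0.1 it is 397.5/400 = 0.994. By this route, a real effect on perinatal mortality would be far smaller than 0.75 suggests.

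**The case against.** **Restriction is not spelled out.** A reader might infer that the article confines perinatal collection to women with a primary outcome and to nobody else. It does not say so in those words. The costly item it names is detailed perinatal data, ward registers are among the sources, and the full protocol is not shown, so all-delivery counts may exist. This part stands as a caution. Still, the sentence in the Discussion names the outcomes themselves and answers the cost of wider collection, so restriction is the natural reading. On either reading the two sections need reconciling.

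**The fall is not automatic.** A reader might infer that any reduction in the primary outcome produces an equal reduction in the perinatal rates. That requires a stable q. The Discussion gives reasons for doubt: hysterectomies may rise while deaths fall, and many complications occur postpartum with no direct bearing on perinatal outcomes. If q differs between components, a change in their mix moves it. This objection stands, and the 0.75 is conditional.

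**The contrast is valid for what it measures.** Over all deliveries, the quantity is the rate of a joint event, a primary outcome together with a perinatal death. Its denominator is not selected by the primary outcome, and 0.75 would be a correct ratio for that event. This also stands: the fault lies in the label and the interpretation, so the effect estimate need not be dropped if it is correctly named.

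**These are secondary outcomes.** The article states why perinatal outcomes were kept out of the primary endpoint and announces no perinatal mortality claim. That limits the reach of the point without removing the conflict.

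**Conclusion.** The definition and the collection rule conflict, and nothing in the article resolves them. If the collection rule governs, the reported figures are bounded at 100 (control) and 75 (intervention) affected women per 10,000 deliveries at the planned rates, and they are not perinatal mortality rates. That conclusion needs no outside figure.

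The size of the spurious effect does need an assumption. With q unchanged, the planned reduction gives a ratio of 0.75 without any change in perinatal risk. A higher q under intervention, or a shift in the component mix, could reduce or cancel it.

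The share of perinatal deaths captured cannot be fixed from the documents. A reader might settle on about 10%, the value at 2.5% overall risk and q of 25% (0.01 × 0.25/0.025), but those assumed ranges already give 6.7% to 15%, and wider ones give 2.5% to 40%.

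The primary outcome, its components, the sample size and the main model are unaffected.

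**What to change.** Reconcile the Perinatal secondary outcomes section with the Discussion in one of two ways.

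1. Redefine both outcomes as stillbirth and neonatal death among women with a primary outcome, and report number and percentage descriptively. No effect should be estimated on this version, because the intervention changes who is in the group. In step 3 above, had the averted cases been those without a stillbirth, the percentage would rise from 20/100 to 20/75 with no additional death.
2. Keep deliveries as the denominator, but name the quantity primary outcome with stillbirth (or with neonatal death). State beside the estimate that it is not an effect on perinatal mortality.

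Report population perinatal rates and effects only if all-delivery counts already exist in the registers. The trial period ended in November 2017, before the article appeared, so new collection is probably impractical.

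The cost is wording and, under the first option, two fewer effect estimates. The trial gives up a claim on perinatal mortality that data collected this way cannot support.

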##### Process evaluation outcomes

The implementation and impact of the intervention in each site was evaluated by both quantitative and qualitative measures. The fidelity, dose, reach and adaptation (whether the intervention is implemented as planned, to the intended population and what amount) was determined by measuring:The duration and content of training and whether it was adapted in different contexts (structured observation of training)The proportion of HCPs working in maternity services that were trained to use the CRADLE deviceThe proportion of facilities with access to working blood pressure devices prior to and after implementationThe number of CRADLE VSA deliveredThe proportion of women attending maternity services that had their blood pressure measured (subset of clusters for a 4-week period immediately prior to implementation and the same duration 3 months after implementation)

The potential impact of the intervention, the acceptability and potential mechanisms of action were explored through the following methods:Semi-structured interviews of a purposive sample of HCPs (*n* = 3–5 in each cluster) at 3 months following implementation explored the experience of triage, intervention, referral and transportation and reception at the higher-level facility, as well as information on the escalation process and barriers to women attending higher-level careA focus group discussion with a purposive sample of stakeholders (*n* = 5–8 in each cluster) at 3 months elicited how the CRADLE VSA influences the process of referrals and work loadGiven our hypothesis that earlier detection will result in earlier referral and management of pregnancy complications, an evaluation of the proportion of women accessing maternity services that were referred to higher-level care was undertaken (for a 4-week period immediately prior to implementation and the same duration 3 months after implementation

The following outcomes were evaluated to explore the potential for the results to be scalable and sustainable:The number of CRADLE VSA reported as broken, lost or stolen (evaluated monthly after implementation to trial end; up to 18 months in the first cluster)The proportion of clinical areas using the CRADLE VSA post implementation (longitudinally assessed according to time of implementation up to 6, 12 and 18 months)Costs of implementation (including equipment, staff, meeting and training, transport)A focus group discussion with a purposive sample of stakeholders (*n* = 5–8 in each cluster) at 6 to 9 months and interviews with the implementation team at 12 months to elicit contextual change over time and sustainability of the intervention

Quantitative process data will be integrated into the outcome datasets to examine whether the effects of the CRADLE intervention differ by implementation. Qualitative methods will capture emerging changes in implementation, experiences of the intervention and unanticipated or complex causal pathways in addition to generating new theory about potential mechanisms of action. Quantitative and qualitative analyses will build upon one another, with qualitative data used to explain quantitative findings, and quantitative data used to test hypotheses generated by qualitative data.

The cost consequence analysis will be modelled on the basis of the equipment required and the health outcomes influenced as recorded in the trial. The incremental financial and economic cost of implementing the CRADLE intervention (device and training package) over the trial will be quantified, thereby evaluating the financial sustainability of the interventions. Research costs will be excluded from the costs of the intervention.

### Cluster description

Each cluster was described according to the number of primary, secondary and tertiary facilities and their referral distances. Details on staffing levels and availability of key resources, such as intensive care beds, blood transfusion and magnesium sulphate use, was collated. In addition, major changes to the trial catchment, such as changes to infrastructure, policy, patient payment requirements or environmental conditions, were systematically reviewed each month.

### Data collection

Methods of data collection were discussed and optimised based on the existing resources available in each site. Outcomes were triangulated across multiple sources (including referral registers, ward registers, patient records, local mortality and morbidity records and active case finding) to ensure data completeness and all outcomes checked to avoid double counting.

Outcome data were recorded over the 20-month period. Consistency and quality of source data was monitored by the research midwife/assistant at each cluster (monthly). Data were entered onto an online database (MedSciNet). This allows for extensive monitoring and query processing features, as well as a comprehensive alerting system to identify missing data. The trial coordinator will monitor data entry continuously on MedSciNet. Ten percent of the source data were validated by the primary investigator and a proportion of this was reviewed by the trial coordinator. Patient records are identified with a unique identification number generated sequentially and no identifying data are stored.

### Method of randomisation

The unit of randomisation is the cluster (or clusters), rather than individual women. Large variation in the primary event rate was anticipated between clusters; therefore, a restricted method of randomisation was used with zero rank correlation between events per month and order of randomisation. The sequence of timing for receiving the CRADLE intervention was determined by computer-generated random numbers by the CRADLE statistician. The clusters were masked to the order of implementation until they are informed of their allocation 2 months prior to their implementation date (to enable training to be arranged).

### Sample size calculation

Sample size estimation has been carried out by the CRADLE statistician, using Stata version 13.1 and the methods of Hemming and Girling [16]. This was informed by data from the feasibility phase. For the purpose of the power calculation an assumption that there are at least 4000 deliveries per centre per month was made (or 8000 per cluster period of 2 months) and at least nine clusters, each observed for 20 months (10 time periods of 2 months each). We anticipated a baseline event rate of 1% and anticipate a 25% reduction in this to 0.75% post intervention. We would require a total of 6300 outcome events, with a coefficient of variation of 0.4 and an Intra Cluster Correlation of 0.0085, to have power of 99%. We would require a total of 2450 outcome events with a coefficient of variation of 0.4, to have power of 95%.

### Statistical plan

The effect of the intervention on the primary outcome, on each of the three components, and on the secondary outcomes specified above, will be reported. Results will be reported firstly as odds ratios (ORs), with risk ratios (RRs) as a secondary comparison if the appropriate models converge. Within the stepped-wedge cluster design it remains appropriate to analyse outcome data from clusters individually, despite randomising cluster time points with some clusters paired [17].

The main statistical analysis method will be by logistic regression, using generalised estimating equations with a population-averaged model [18] (Stata command xtgee) with fixed centre effects and separate fixed linear trends in each centre for changes in outcome over time. Autoregressive correlation will account for decreasing correlations between observations over time. This model outperformed the multilevel model structure of Hussey and Hughes [19], being apparently less susceptible to bias. It gives equal weight to each woman, rather than each centre, and (being population-averaged) reports effects averaged over the length of the trial. Simulations studies suggest that using time categories, rather than linear trends do not correct well for separate time trends by centre, and can cause convergence problems. Results will be expressed as ORs; at the low event rates expected (≤ 5%), ORs and RRs are reasonably close (in the simplest case, for 5% and 3.75%, RR = 0.75, OR = 0.74). A secondary analysis to obtain RRs using a log link will be attempted, but simulation studies suggest that the convergence may be poor. We will adjust for centre effects and linear time trends and the interaction between them. This will effectively adjust for differences in baseline availability of resources between clusters.

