#### Design and study setting

The CRADLE-3 trial was a pragmatic, mixed-methods, multicentre, stepped-wedge cluster-randomised controlled trial of the introduction of the CRADLE intervention (CRADLE VSA device and CRADLE training package) to routine maternity care settings in LMICs. It was informed by the MRC guidance for evaluation of complex interventions [11].

Ten clusters were identified to take part in the trial. Each cluster comprised a secondary or tertiary health facility with multiple satellite primary care centres that referred to the central hospital:Gokak, Belgaum, IndiaHarare, ZimbabweNdola, ZambiaLusaka, ZambiaFree Town, Sierra LeoneMbale, UgandaKampala, UgandaCap Haitien, HaitiSouth West, MalawiAddis Ababa, Ethiopia

Each randomisation cluster crossed over from control to the CRADLE intervention at 2-monthly intervals (Figs. 1 and 2 and Additional file 1). At the time each cluster was randomised to receive the CRADLE intervention, all levels of healthcare providers within that cluster, involved in the care of pregnant/postpartum women, had access to the CRADLE intervention. The intervention effect will be determined by comparing data points in the intervention section of the wedge with those in the controlled section.

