#### CRADLE training package

The intervention users included every cadre of healthcare professional involved in maternity care within the cluster. This included community healthcare providers (cHCPs) where they were supported at district level and involved in provision of routine maternity care. The CRADLE research group created a simple CRADLE training package for prospective CRADLE VSA users.

The training package consisted of short animated films, an interactive session, action prompt cards attached to the CRADLE VSA and posters. There were two sets of training materials available, one for facility HCP (fHCPs) and one for cHCP with very limited resources or no formal training. All materials were translated into local language where required.

The CRADLE package content covered:How to use the CRADLE VSAMaintenance of the CRADLE VSABasic overview of clinical assessment and management of pre-eclampsia/eclampsia and shock in relation to the traffic-light alerts

At the randomised time point the local implementation team (clinical research officers responsible for ongoing CRADLE outcome data collection and site principal investigators) attended face-to-face one-off training with the research team lasting approximately 5 h. The implementation team and research team subsequently delivered one-off group training sessions lasting 2–4 h to local stakeholders and representative HCP from each of the clinical areas in the cluster.

Attendees were given training materials and CRADLE VSA to disseminate to their clinical areas. The implementation team continued to visit clinical areas regularly to collect outcome data therefore providing ongoing support to HCP.

The core components of the intervention (the CRADLE VSA, animated films, posters and content of the training presentation) were standardised across all clusters. Delivery of the core components could be adapted to meet the needs of the cluster.

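### The main model's intervention odds ratio is an average over the trial only if the effect is immediate and constant, and the Statistical plan states it without that condition

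*Protocol article*

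**What the plan says.** The Statistical plan section of the protocol article specifies logistic regression by GEE "with fixed centre effects and separate fixed linear trends in each centre for changes in outcome over time", and restates this as "We will adjust for centre effects and linear time trends and the interaction between them". On correlation it says "Autoregressive correlation will account for decreasing correlations between observations over time"; no value is given. It then says that the model, "being population-averaged) reports effects averaged over the length of the trial".

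The intervention contrast is described under Design and study setting: "The intervention effect will be determined by comparing data points in the intervention section of the wedge with those in the controlled section". I read this as a single 0/1 term that switches on at crossover. No term for time since crossover is named.

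Two other sections bear on whether the effect could change with exposure. Under CRADLE training package, training sessions are one-off and "Attendees were given training materials and CRADLE VSA to disseminate to their clinical areas". Under Process evaluation outcomes, "The number of CRADLE VSA reported as broken, lost or stolen" is counted monthly after implementation, and the proportion of clinical areas using the device is followed up to 18 months.

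**The concern.** The sentence gives a reason (population-averaged) for a property (averaging over the trial), and the reason does not deliver it. A marginal GEE averages over clusters. How the effect is averaged over time is decided by the mean model, which here has one step plus time trends.

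If the effect builds up after crossover, the trend terms take up much of the gradual part, and the step is determined mainly by the first months, when the effect is smallest. If the effect wanes, the step reflects the early, larger effect. A reader told that the OR is a trial-long average could take an OR near 1 as no benefit when there was an average benefit, or take a strong OR as durable when it was not. The trial's aim is a reduction of at least 25%, so this affects how the primary result is read.

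**Working it through.** **The plan's own figures.** For 5% and 3.75% the OR is (0.0375/0.9625)/(0.05/0.95) = 0.740, as the plan states. For the planned 1% to 0.75% it is (0.0075/0.9925)/(0.01/0.99) = 0.748, so the log OR is −0.290. The sample size section assumes "at least nine clusters, each observed for 20 months (10 time periods of 2 months each". At 8000 deliveries per period and a mean rate of 0.875%, this gives 9 × 10 × 8000 × 0.00875 = 6300 events, again as stated.

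**Set-up.** From the protocol: 10 clusters, 20 months, 2-monthly steps, 4000 deliveries per centre-month, full OR 0.748. Assumed: crossovers after months 2, 4, 6, 8, 10, 10, 12, 14, 16 and 18; a 1% baseline in every centre; no underlying trend. The number of exposed cluster-months is 18 + 16 + 14 + 12 + 10 + 10 + 8 + 6 + 4 + 2 = 100.

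**Effect shapes.** In exposure month e, the share of the full log OR is min((e − 0.5)/L, 1) for a build-up over L months, 0 then 1 for a lag, and max(1 − (e − 0.5)/12, 0) for waning.

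**True average.** This is exp(−0.290 × mean share over exposed cluster-months).
- 2-month lag: 20 of the 100 months have no effect, so exp(−0.290 × 0.80) = 0.793.
- 6-month build-up: the shares sum to 71.7, so exp(−0.290 × 0.717) = 0.812.

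**Fitted value.** The planned model (centre effects, a linear trend per centre, one step) was solved on the expected monthly proportions at working independence.

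| Effect after crossover | True average OR | Main-model OR |
|---|---|---|
| Immediate, constant | 0.748 | 0.748 |
| Build-up over 3 months | 0.781 | 0.855 |
| Build-up over 6 months | 0.812 | 0.930 |
| Build-up over 12 months | 0.867 | 0.991 |
| 2-month lag | 0.793 | 0.904 |
| 4-month lag | 0.835 | 1.005 |
| Waning over 12 months | 0.863 | 0.758 |

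With an autoregressive working correlation of 0.8 (assumed), the 6-month build-up gives 0.981 and the 2-month lag 1.003.

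**Why.** In a linear approximation, the step coefficient weights each exposed month by the residual of the step indicator after regression on centre and centre trend. With the paired clusters placed at the first step instead (108 exposed cluster-months), months 1–6 are 54/108 = 50% of exposed time but carry 117% of the weight. Months 10–18 together carry about −24%. Months 1 and 2 carry 0.319 + 0.283 = 0.602, so a 2-month lag should give about exp(−0.290 × 0.398) = 0.891. The fit in that layout, with assumed baselines of 0.4% to 1.8%, gives 0.898.

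**Is it the centre-specific trends?** No. With a common linear trend or 2-month period categories and the same step, the 6- and 12-month build-ups give about 0.91 and 0.98.

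**Power.** The model-based standard error is about 0.045 on the log OR. For the 6-month build-up, |ln 0.930|/0.045 = 1.61, so power at two-sided 5% (assumed) is Φ(1.61 − 1.96), about 36%.

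**Supporting analysis.** Keep the centre effects and centre trends, and replace the step with 2-month time-since-crossover categories averaged by exposed time. The 6-month build-up then gives 0.821 against 0.812, with a standard error of about 0.08. Power is Φ(|ln 0.821|/0.08 − 1.96) = Φ(0.50), about 69%.

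**The case against.** The strongest reply is that the protocol describes an abrupt switch. All levels of provider had access at the randomised time, most pre-existing devices were removed, and clusters had 2 months' notice to arrange training. If the effect is immediate and constant, the model returns 0.748 exactly and the sentence does no harm. This stands: a reader might infer that the plan itself expects the effect to change, and it does not say so. Spread through attendees and tracking of device loss make change plausible. The length of any build-up or lag is my assumption.

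A reader might also infer that any gradual uptake would be reported as no effect. The figures do not support that. A 3-month build-up is attenuated to 0.86, not erased. A near-null OR needs slow build-up, a lag of about 4 months, or strong working autocorrelation.

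Nor should the centre-specific trends be blamed or dropped. The plan wants them because trends may differ by centre, and that is sound. With a true constant OR of 0.748 and assumed centre slopes of SD 0.2 log-odds per year, an exposure-time model with common period effects gave averages from 0.61 to 0.91 (95% of 300 draws, no sampling noise). The planned model gave 0.748 every time.

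Finally, the plan will examine whether effects differ by implementation, and exposure-time sensitivity analyses are commonly left to an analysis plan that is not shown. Their absence is therefore no fault here. But the sentence is a positive, unconditional statement about what the main result means, and neither point corrects it.

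**Conclusion.** The sentence is wrong as an unconditional statement and should be corrected. The main model remains usable, and its coefficient is the effect under the assumption that the effect is immediate and constant. If that assumption fails, the coefficient mainly reflects the first months after crossover. Build-ups of 3, 6 and 12 months are reported as 0.86, 0.93 and 0.99 against true averages of 0.78, 0.81 and 0.87. Waning over 12 months is reported as 0.76 against 0.86.

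These sizes rest on the assumed crossover layout, equal baselines, no secular trend, working independence and the chosen effect shapes. Another pairing changed the ORs by less than 0.01. A separate run with varied baselines and a slightly faster ramp showed the same pattern (6 months: 0.90 against 0.80). Stronger working correlation enlarged the gap for build-ups and lags.

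**What to change.** 1. Delete the claim, or replace it with wording such as: *the odds ratio is marginal over clusters; it equals the average effect over exposed time only if the effect is immediate and constant after crossover.* Keep the main model.
2. Pre-specify a supporting analysis with the same centre effects and centre-specific linear trends, with the step replaced by 2-month time-since-crossover categories. Report their exposed-time-weighted average with its confidence interval.
3. State that a near-null main-model OR does not by itself exclude a benefit that builds up.
4. If a version with common period effects is shown, label it a further sensitivity analysis and note that it is biased when time trends differ by centre. Dropping the first 2 months after crossover helps only with short lags: it still gives 0.83 to 0.85 for the 6-month build-up (depending on how the ramp is coded) and 0.94 for the 12-month one.

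**Cost.** Wording and one extra model on data already collected. The supporting estimate is less precise: a standard error of about 0.08 against 0.045 at the planned size, or 75–80% larger. Power for a constant 25% reduction would still be Φ(0.290/0.08 − 1.96), about 95%, if the model-based standard error holds. The last exposure category rests on a single centre in the assumed layout, so the weighted average should be read rather than individual late categories.
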